## Abstract

**Background:**

Age is considered as one of the most important risk-factor for many types of solid and hematological cancers, as their incidence increases with age in parallel to the ever-growing elderly population. Moreover, cancer incidence is constantly increasing as a consequence of the increase in life expectancy that favors the process of cellular senescence. Geriatric assessment has been increasingly recognized as predictive and prognostic instrument to detect frailty in older adults with cancer. In particular, the G8 score is a simple and reproducible instrument to identify elderly patients who should undergo full geriatric evaluation. Due to their frailty, elderly patients may be often under-treated and a therapeutic choice based also on a comprehensive geriatric assessment (CGA) is recommended. With these premises, we aim to test the impact of the CGA based interventions on the quality of life (QoL) of frail elderly onco-hematological patients, identified by the G8 screening, candidate for innovative target directed drugs or treatments including the combination of radiotherapy and chemotherapy (RT + CT).

**Methods:**

Patients aged > 65 years, candidate to target directed agents or to RT + CT treatments are screened for frailty by the G8 test; those patients classified as frail (G8 ≤ 14) are randomized to receive a CGA at baseline or to conventional care. The primary endpoint is QoL, assessed by EORTC QLQ-C30C. As collateral biological study, the potential prognostic/predictive role of T-cell senescence and myeloid derived suppressor cells (MDSC) are evaluated on plasma samples.

**Discussion:**

This trial will contribute to define the impact of CGA on the management of frail elderly onco-hematologic patients candidate to innovative biological drugs or to integrated schedules with the association of RT + CT. Furthermore, the use of plasma samples to assess the potential prognostic value of imbalance of immune-competent cells is expected to contribute to the individualized care of elderly patients, resulting into a fine tuning of the therapeutic strategies.

**Trial registration:**

ClinicalTrials.gov ID: NCT04478916. registered July 21, 2020 – retrospectively registered.

## Background

Age is considered as one of the most important risk-factor for many types of solid and hematological cancers, as their incidence increases with age in parallel to the ever-growing elderly population [1]. The progressive increase of life expectancy facilitates the accumulation of cellular dysfunctions including “cell senescence”, indirectly favoring carcinogenesis [2, 3], because some of the mechanisms involved in aging are also involved in age-related diseases such as cancer [4].

Elderly patients often require tailored and different strategies compared to their younger counterparts [5–7]. In fact, aging is associated with decreased physiological reserves and altered pharmacokinetics, reducing treatment tolerability and enhancing the risk of treatment-related adverse events. Moreover, goals and priorities may indeed differ greatly according to age when making treatment decisions and preserving health-related quality of life (HRQoL).

It must be also taken into account that in the elderly onco-hematological patient, host dependent factors, such as those related to immunosenescence may interfere with treatment efficacy through the induction of immunosuppression mediated by myeloid derived suppressor cells (MDSC) in different inflammatory conditions [8–10]. Moreover, cellular senescence, a highly dynamic, multi-step process, during which the properties of senescent cells continuously evolve and diversify, may interfere with drug sensitivity, ending in an unfavorable prognosis [11, 12].

Recent guidelines by the American Society of Clinical Oncology (ASCO) strongly recommend a minimum core of geriatric assessment based on the evaluation of function, comorbidity, falls, depression, cognition, and nutrition in all patients who are candidates for oncological treatments [13]. Current guidelines by the Italian Association of Medical Oncology (AIOM) recommend the administration of a Comprehensive Geriatric Assessment (CGA) to all patients who are aged 70 years or older and who screen positive at screening tools such as the G8 or the Vulnerable Elders Survey-13 (VES-13) [14, 15].

In the perspective of a global care of the oncologic elderly patient, the use of a screening test for vulnerability represents a first step to streamline decisions: G8 has demonstrated such ability to identify patients requiring a dedicated CGA, with a threshold of ≤ 14/17 and a strong 1-year prognostic value [16].

Due to the possible complexity of their clinical conditions and comorbidities, elderly patients are often underrepresented in clinical trials; thus, a major challenge in oncology, as well as an unmet need, is to increase the relevance of clinical trials in older patients, to improve research in the field of geriatric oncology and to promote translational studies on the interface between aging and cancer.

We designed the ONCO-Aging study to fill this gap of knowledge; the primary objective is to optimize the care of elderly and frail onco-hematological patients, candidate to innovative target directed agents or to combined schedules including radiotherapy (RT) and chemotherapy (CT), since the accrual of this type of patients in clinical trials is limited.

## Methods/design

The ONCO-Aging study is part of a larger project (AGING Project) funded by the Italian Ministry of University and Research (MIUR), which has awarded a number of university departments as “departments of excellence” for research. The AGING Project is a project of excellence launched by the Department of Translational Medicine at the Università del Piemonte Orientale (UPO), Novara, IT, aimed to provide effective solutions to the emerging scientific and social challenges brought by aging. This project is based on four main pillars: (i) interdisciplinary approach, (ii) bench-to-bedside research, (iii) support to research and education, and (iv) public engagement. The AGING Project includes the activation of a biobank. The biobank is a research facility established by UPO to foster an inclusive scientific community where citizens, researchers and institutions come together to actively participate in the research process. The AGING Project will use the UPO biobank for the “Novara Cohort Study,” a study aimed to investigate the aging processes in the population residing in the Novara area and to identify lifestyles leading to healthy aging and risk factors associated with aging-related diseases.

### Study Design

The ONCO-Aging study is a prospective, randomized study and includes a clinical trial and a collateral biologic study. Patients older than 65 years, with hematological or oncological neoplasms, who refer for treatment to the Oncology, Hematology and Radiation Oncology Divisions of the University Hospital Maggiore della Carità in Novara, IT, and candidate to therapies with innovative target directed agents or to combined schedules including RT and CT, are screened for frailty by the G8 questionnaire; according to previous evidence, a score ≤ 14/17 is considered the threshold for frailty [16, 17]. Targeted directed agents include the following drugs: tyrosine-kinase inhibitors (TKis), monoclonal antibodies and immune checkpoint inhibitors (ICIs), alone or in combination schedules with CT. Combined treatment schedules including RT and CT are also included. Patients with a G8 score ≤ 14/17, are randomized in a 1:1 ratio to the following procedures: arm A, onco-geriatric evaluation by CGA; arm B, standard clinical care, according to local practice. Figure 1 shows the flowchart of the study. Patients are randomized by a REDCap dedicated system. Patients assigned to arm A undergo a CGA at baseline, before treatment start and every 6 months thereafter and may receive a CGA based geriatric intervention if required according to the geriatrician judgement (Fig. 2). Patients in arm B are managed according to clinical practice (Fig. 3). Blood samples to assess the prognostic and predictive value of cell-derived data (MDSC and T cell senescence) and their modification with treatment, will be collected at baseline and at the time of disease progression. Blood samples from healthy, age-matched controls, are recruited on a voluntary basis and also from the UPO Biobank.

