### Statistical design

The sample size was estimated by a two-tailed t-test (alpha = 0. 05, power = 0. 8 and an effect size Cohen (ES) equal to 0. 5) for a minimum clinically relevant difference of 10 points (SD = 20) on the global EORTC QLQ C30 Quality of Life scale. The planned sample size is 144 patients (72 per arm), considering a 10 % loss at follow-up. The primary endpoint will be evaluated on the ITT population. Baseline data will be summarized in terms of mean, standard deviation, median, I and III quartile, for continuous variables, and percentages for categorical variables. A test for the difference between two queued averages will be applied when comparing the total score for QoL. A level of significance of 5 % will be considered statistically significant. The study is expected to enroll about 144 patients with solid tumor neoplasms or hematological malignancies candidate to a first line treatment for advanced disease.

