Likewise, it can be speculated that the biological age measured by the CGA and expressed in terms of fitness, unfitness and frailty could be related to a progressive inefficiency of the immune system, that might be predominant in frail patients. This hypothesis derives from the observation that in patients with solid and hematological malignancies, CGA-defined frail patients seem not to benefit from potentially life-saving therapies compared with younger counterparts [20]. Many studies provided evidence that the unfavorable outcome of elderly patients is partly related to clinical and biological differences in the disease itself, such as a more aggressive phenotype, more frequent advanced stage and presence of symptomatic disease [30]. To clarify this aspect, we added a biological aspect in our study to evaluate the role of T cell senescence and MDSC in our cohort of frail patients and to investigate the possible relationship among age, immune senescence and frailty.

Our trial has some limitations. It is a monocentric exploratory study, with a limited number of patients with different solid and hematologic tumors. The different types of diseases that can be included usually have different timepoints for the radiological and clinical evaluations, but as a starting protocol, we decided to identify standard timepoints visits for geriatric and radiologic evaluations, according to local clinical practice and guidelines. On the other side, given the network organization of the “Rete Oncologica Piemontese”, where the University Hospital Maggiore della Carità in Novara, IT, is the second most important hub in the region, and therefore is allowed to prescribe innovative oncological treatments and to perform aggressive combination therapies with the association of RT and CT, the probability of poor compliance or drop out during follow up is minimal. This eventuality is also further reduced by the regular introduction of palliative simultaneous care in frail patients of any age, being our center an ESMO designated center for simultaneous care. The results of the ONCO-aging study, dedicated to the elderly patient population, will be used to define a global strategy within the “UPO AGING project”, to improve our aging-specific research with a multicenter study including a larger number of patients and a more selective division by cancer type and treatments.

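### The primary QoL test leaves out disease group and planned treatment route, two known sources of spread; it is valid and correctly sized, but adjusting for them would give a modest, almost free gain in precision.

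*Protocol article*

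**What the plan says.** Under Study Design, the article recruits from three divisions (Oncology, Hematology and Radiation Oncology). It admits patients due to receive tyrosine-kinase inhibitors, antibodies or checkpoint inhibitors, with or without CT, or combined RT and CT. Study Population adds that solid tumours must be advanced, whereas haematological cancers may be at any stage.

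On allocation, Study Design says: "Patients with a G8 score ≤ 14/17, are randomized in a 1:1 ratio to the following procedures". It adds that a REDCap system is used. It does not say whether the list is simple, blocked or stratified.

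Under Statistical design, "The sample size was estimated by a two-tailed t-test" with "power = 0. 8 and an effect size Cohen (ES) equal to 0. 5". The analysis is then fixed: "A test for the difference between two queued averages will be applied when comparing the total score for QoL". I read this as a two-sided test of the difference between two means. No disease, treatment or baseline term is named.

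The Discussion concedes that the trial has "a limited number of patients with different solid and hematologic tumors" and leaves "a more selective division by cancer type and treatments" to a later multicentre study.

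**The concern.** Diagnosis and intended treatment are eligibility criteria, so both are on file for every patient before randomisation. The stated analysis does not use them. If QoL on treatment differs between RT + CT and targeted agents, or between solid and haematological disease, that difference is counted as random variation in the primary test.

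The baseline questionnaire is completed before treatment starts. It can absorb group differences already present then, but not all of a treatment-related change that comes later and differs by route.

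What is at stake is precision: a somewhat wider confidence interval than the collected data allow. The Discussion treats the mix as something only a later study can address, yet part of it can be handled in this trial's own model.

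**Working it through.** **Inputs from Statistical design:** difference 10 points, SD 20, two-sided alpha 0.05, power 0.80, 10% loss, 144 patients (72 per arm). **Assumed, because the documents give no figure:** share p of patients in the smaller route, 20% to 50%; QoL gap g between routes, 5 to 20 points; SD 20 is the SD of the whole mixed population.

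**1. The plan's own figure.** Standardised effect 10/20 = 0.5. A two-sided two-sample t-test needs 63.8, so 64 per arm. With 10% loss, 64/0.90 = 71.1, so 72 per arm and 144 in total. This reproduces exactly. Power with 64 evaluable per arm is 80.1%.

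**2. Effect of adjusting for route.** The between-route part of the variance is p(1 − p)g². The residual SD after adjustment is √(400 − p(1 − p)g²). Power is from the noncentral t with 64 per arm and effect 10/(residual SD).

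| Share p | Gap g | p(1 − p)g² | Residual SD | Power |
|---|---|---|---|---|
| 50% | 5 | 6.25 | 19.84 | 80.8% |
| 50% | 10 | 25 | 19.36 | 82.6% |
| 50% | 15 | 56.25 | 18.54 | 85.7% |
| 50% | 20 | 100 | 17.32 | 90.0% |
| 20% | 5 | 4 | 19.90 | 80.5% |
| 20% | 10 | 16 | 19.60 | 81.7% |
| 20% | 15 | 36 | 19.08 | 83.7% |
| 20% | 20 | 64 | 18.33 | 86.5% |

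These figures are for route alone. The same formula applies to disease group, with its own share and gap. They do not include the gain from the baseline score, which may overlap with them.

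**3. Error rate and power by simulation** (50:50 routes, total SD 20, 64 per arm, 20,000 runs per cell).

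| Allocation | Test | Type I error, gap 10 / 20 | Power, gap 10 / 20 |
|---|---|---|---|
| Unstratified | Unadjusted | 5.0% / 4.9% | 80.1% / 80.3% |
| Unstratified | Adjusted | 5.0% / 5.1% | 82.2% / 89.6% |
| Stratified by route | Unadjusted | 4.2% / 2.4% | 81.0% / 83.4% |
| Stratified by route | Adjusted | 4.9% / 5.1% | 82.9% / 90.3% |

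The unadjusted test is correct under unstratified allocation and conservative under stratified allocation. The adjusted test holds 5% under both and has more power under both.

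**4. Chance imbalance, if allocation is unstratified.** The SD of the between-arm difference in route share is √(2p(1 − p)/64), which is 8.8 percentage points at p = 50%. The resulting 95% range of shift in the estimate is 1.96 × 0.088 × g: about ±1.7 points for a 10-point gap and ±3.5 for a 20-point gap. The standard error of the arm difference is 20 × √(2/64) = 3.5 points and already includes this component.

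**The case against.** The strongest reply is that nothing here is wrong. The test matches the one used for sizing, keeps its 5% level under unstratified allocation and has its planned 80% power. Covariates are often left to an analysis plan, and the authors disclose the heterogeneity. All of this stands. It limits the point to an improvement in precision; it does not remove it, because the article states a specific unadjusted test and that choice can be bettered at almost no cost.

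A reader might infer three stronger things, none of which the documents support:

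- **That allocation ignores disease group and route.** The article is only silent. A condensed article may leave stratification factors to the full protocol, which is not shown.
- **That chance imbalance in route biases the result.** It averages zero over randomisations and is already in the standard error, as steps 3 and 4 show.
- **That the trial is underpowered.** Power falls below 80% only if SD 20 is a within-route figure. With a 30% share, the total SD would be √(400 + 21) = 20.5 at a 10-point gap and √(400 + 84) = 22.0 at 20 points, giving 78% and 72%. Statistical design gives one SD for the whole population and mentions no route, so the total-SD reading is the natural one.

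Two further cautions are fair. CT can occur in both routes, so the two-way split may explain little of the spread. A 20-point gap is twice the trial's own minimum relevant difference, so the top of the range is generous.

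**Conclusion.** The point holds as a modest gain in precision. The primary test is valid and 144 patients is the right number for its stated assumptions. Leaving out disease group and planned route puts any QoL difference between those groups into the error term.

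With total SD 20, 64 evaluable per arm and 20–50% of patients in the smaller route, adjusting for route lifts power from 80% to about 81% at a 5-point gap, 82–83% at 10 points and 86–90% at 20 points. The true shares and gaps are unknown from the documents, so the lower figures are as plausible as the upper ones. The benefit of adding disease group cannot be put in numbers without its own share and gap.

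The recommendation does not depend on how REDCap allocates. Without stratification, adjustment recovers precision; with stratification, it also brings the test back to its nominal 5% level.

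**What to change.** In Statistical design, replace the comparison of two averages with a linear model for the primary QoL score containing arm, disease group (solid or haematological), treatment route planned at randomisation (targeted agent with or without CT, or RT + CT) and the baseline QLQ-C30 score. Keep the two-sided 5% test on the arm term.

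Use the planned route, not the route received. In arm A the geriatric assessment comes before treatment starts, so a treatment change that it prompts is part of the effect and should not be adjusted away.

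State whether allocation is stratified, and include in the model any factor used to stratify it.

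The cost is wording and three degrees of freedom: 128 evaluable patients leave 126 in the two-group test and 123 in this model. Two of the three are for disease group and route, and one is for the baseline score. No extra patients or data are needed. Trial status reports 63 of 144 patients randomised, so at that stage the model could still be fixed before the primary comparison.

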**Fig. 1 Fig1:**
[figure not shown]
Prospective, observational, randomized study. Patients will enter the trial after completion the screening phase. Only patients aged ≥ 65 years and whose resulted as fragile using G8 screening tool with a score ≤ 14/17, will be randomized into 2 arms; Arm A: will be evaluated by Comprehensive Geriatric Assessment (CGA); Arm B: Control group. Both arms will be evaluated for their quality of life using EORTC – QLQ-C30 questionnaire, aiming to develop an accurate index for elderly patients with onco-hematological tumors using the CGA as primary study endpoint

**Fig. 2 Fig2:**
[figure not shown]
SPIRIT (Standard Protocol Items: Recommendations for Interventional Trials) diagram for ARM A: Geriatric Intervention Group; schedule of enrollment, interventions, and assessments. Abbreviations: M3; 3 months after randomisation, M6; 6 months after randomisation, M9; 9 months after randomisation, M12; 12 months after randomisation, PD; at progression

**Fig. 3 Fig3:**
[figure not shown]
SPIRIT (Standard Protocol Items: Recommendations for Interventional Trials) diagram for ARM B: Control Group; schedule of enrollment, interventions, and assessments. Abbreviations: M3; 3 months after randomisation, M6; 6 months after randomisation, M9; 9 months after randomisation, M12; 12 months after randomisation, PD; at progression

### Objectives

The primary objective of the ONCO-Aging study is to assess the impact of the CGA and related interventions on the Quality of Life (based on the EORTC QLQ C30 questionnaire) of onco-hematological patients, with a G8 score ≤ 14/17, candidate to innovative target agents or integrated RT and CT schedules. Secondary objectives: *1.* to assess the percentage of treatment modifications, due to toxic events, in those patients who receive CGA assessment and related interventions, compared with those treated according to local clinical practice; 2) to evaluate the impact of CGA and related interventions on patient outcome and treatment adherence, as compared to those in the control arm.

The aim of the biological study is to assess the presence and the modifications induced by treatments of senescent T cell and MDSC in the peripheral blood of enrolled patients in both arms to evaluate the correlation with treatment efficacy and patient characteristics, including comorbidities, concomitant drugs, and lifestyle habits.

The primary endpoint is Health Related Quality of Life, based on the EORTC QLQ C30 questionnaire [18]; EORTC QLQ C30 questionnaire will be administered at baseline and every 3 months during treatment/follow up.

### Statistical design

The sample size was estimated by a two-tailed t-test (alpha = 0. 05, power = 0. 8 and an effect size Cohen (ES) equal to 0. 5) for a minimum clinically relevant difference of 10 points (SD = 20) on the global EORTC QLQ C30 Quality of Life scale. The planned sample size is 144 patients (72 per arm), considering a 10 % loss at follow-up. The primary endpoint will be evaluated on the ITT population. Baseline data will be summarized in terms of mean, standard deviation, median, I and III quartile, for continuous variables, and percentages for categorical variables. A test for the difference between two queued averages will be applied when comparing the total score for QoL. A level of significance of 5 % will be considered statistically significant. The study is expected to enroll about 144 patients with solid tumor neoplasms or hematological malignancies candidate to a first line treatment for advanced disease.

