### Study procedures

Comprehensive Geriatric Assessment (CGA): in arm A, patients receive a dedicated geriatric examination (60–90 min), administered by a dedicated geriatrician, and are classified according to CGA results and the Rockwood Frailty Index (RFI) as “frail” (RFI > 0.25), “unfit/prefrail” (0.08 > RFI < 0.25) or “fit” (< 0.08) [19].

The CGA includes evaluation of cognitive status with the Mini Mental State Examination (MMSE), Clock drawing test (CDT), and Montreal Cognitive Assessment (MOCA) [20]; of psychosocial status by the means of Geriatric Depression Scale (GDS) and Social Vulnerability Index (SVI) [21]; of disability by Activities of Daily Living (ADL) and Instrumental Activities of Daily Living (IADL) [22, 23]; of nutritional status by Mini Nutritional Assessment (MNA) [24]; of comorbidities by Cumulative Illness Rating Scale for Geriatrics (CIRS-G) and of pharmacological impact by number of drugs [25]; of sarcopenia and physical performance by Hand Grip Strength, Timed Up and Go test, Tinetti Scale, and number of falls in last six months [26]. CGA is performed at baseline and every 6 months. If issues are found in the areas of fragility, mid-term evaluations are foreseen, as indicated by the geriatrician. CGA based interventions will cover nutritional imbalance, social issues including the availability of caregiver and psychological interventions by dedicated psyco-oncologists.

In both arms, QoL assessment by the standardized EORTC QLQ-C30 questionnaire is performed at baseline (before treatment start) and every 3 months. Disease evaluation is performed in both arms according to local clinical practice. Patients are observed for up to 12 months or until disease progression (Fig. 4).

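### The stated primary QoL test makes no use of the baseline QLQ-C30; adjusting for it would be a free gain in precision, although the planned test is valid

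*Protocol article*

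**What the plan says.** All of the statistical text is in the Statistical design section of the protocol article. The trial is sized as follows: "The sample size was estimated by a two-tailed t-test (alpha = 0. 05, power = 0. 8", for a "minimum clinically relevant difference of 10 points (SD = 20) on the global EORTC QLQ C30 Quality of Life scale". This leads to "The planned sample size is 144 patients (72 per arm), considering a 10 % loss at follow-up". The analysis sentence is "A test for the difference between two queued averages will be applied when comparing the total score for QoL", at a 5% significance level. The only use the section states for baseline data is descriptive summary.

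Under Study procedures, the schedule for the outcome is "In both arms, QoL assessment by the standardized EORTC QLQ-C30 questionnaire is performed at baseline (before treatment start) and every 3 months"; the Objectives section says the same. The legends of Figures 2 and 3 define 3, 6, 9 and 12 months after randomisation, and progression, as timepoints. Under Study Design, patients "are randomized in a 1:1 ratio to the following procedures" through REDCap, and no stratification is mentioned. The article mentions no baseline adjustment, change from baseline or repeated-measures model.

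**The concern.** A patient's QoL score before treatment would be expected to predict the later score. The trial collects it in both arms, yet the analysis sentence compares two averages with no baseline term. The population mixes advanced solid tumours with haematological cancers at any stage, and targeted agents with combined radiotherapy and chemotherapy, so baseline QoL can be expected to vary.

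Two things are at stake. The first is precision: variation that baseline would explain stays in the error term. The second is the single realised trial: if the arms differ at baseline by chance, part of that difference passes into the estimated effect and nothing removes it.

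**Working it through.** **Inputs from the Statistical design section.** Two-sided alpha 0.05, power 0.80, difference 10 points, SD 20 (so d = 10/20 = 0.5), 10% loss, 72 per arm. The 1:1 allocation is from Study Design.

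**Assumed input.** The correlation ρ between baseline and follow-up scores is not in the documents. It is varied from 0.3 to 0.7, with SD 20 at both times.

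**Step 1: the plan's own figure.** A two-sided two-sample t-test with d = 0.5, alpha 0.05 and power 0.80 needs 63.77, so 64 per arm. Allowing for loss, 64/(1 − 0.10) = 71.1, so 72 per arm and 144 in total. The stated size is reproduced exactly. Power at 64 per arm is 80.1%.

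**Step 2: power with baseline as covariate.** The residual SD is 20 × √(1 − ρ²). Using it in the same t-test calculation at 64 evaluable per arm, for a 10-point difference:

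| ρ (assumed) | Residual SD | Power |
|---|---|---|
| no adjustment | 20.0 | 80.1% |
| 0.3 | 19.08 | 83.7% |
| 0.4 | 18.33 | 86.5% |
| 0.5 | 17.32 | 90.0% |
| 0.6 | 16.00 | 93.9% |
| 0.7 | 14.28 | 97.6% |

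At ρ = 0.5 the confidence interval is √(1 − 0.25) = 0.866 times as wide, about 13% narrower. That equals 64/0.75 = 85.3, or about 85 patients per arm without adjustment.

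**Step 3: chance imbalance.** The standard error of the baseline mean difference is 20 × √(2/64) = 3.54 points, so its 95% range is ±1.96 × 3.54 = ±6.9 points. The probability of an imbalance above 5 points in either direction is 0.157, about 16%. An imbalance of B points shifts the unadjusted estimate by about ρ × B. For B = 5 the shift is 1.5 points at ρ = 0.3, 2.5 at 0.5 and 3.5 at 0.7.

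**Step 4: could imbalance alone produce 10 points?** At ρ = 0.5 this needs 10/0.5 = 20 points at baseline, which is 20/3.54 ≈ 5.7 standard errors. At ρ = 0.7 it needs 10/0.7 = 14.3 points, about 4 standard errors. It is practically excluded.

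**Step 5: is a change score enough?** The SD of change is 20 × √(2(1 − ρ)). Power at 64 per arm is 66% at ρ = 0.3, 80% at 0.5 and 95% at 0.7. It is below the covariate-adjusted power in each case, and at ρ = 0.3 it is below that of the unadjusted test.

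**The case against.** The strongest reply is that nothing in the plan is statistically wrong. Under randomisation the unadjusted test keeps its 5% error rate and is unbiased on average. It matches the sizing method and delivers the stated power. Heterogeneity of tumours and treatments acts through the outcome SD, and the plan already assumes 20. All of this stands.

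A second reply is that a condensed article commonly leaves covariates and model form to a fuller document, and that one sentence does not exclude adjustment. This stands in part: an unseen analysis plan may already adjust. But the article does not stay silent on the method. It names a test that agrees with the t-test used for sizing, and the only use it states for baseline data is descriptive. The point concerns what is stated.

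A reader might infer three stronger things that the documents do not support.

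- *The test is unrecognisable because of the odd adjective before the averages.* The same section sizes the trial with a two-tailed t-test, so the word is most plausibly a mistranslation of tailed.
- *Chance imbalance could easily mimic the planned effect.* The working shows that it could hardly do so.
- *Adjustment would make up for heavy attrition.* The article plans for 10% loss and expects minimal drop-out in its Discussion; it gives no larger loss to work from. Added precision would in any case not cure non-random dropout.

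**Conclusion.** This is a worthwhile improvement at no data cost, not an error that invalidates the plan. The sample size is right for the test stated. Adjustment would bring power at 64 evaluable per arm from 80% to between 84% and 98%, and would remove a possible shift of about 1.5 to 3.5 points for a 5-point baseline imbalance.

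These figures rest on the plan's SD of 20, taken as equal at baseline and follow-up, and on a correlation of 0.3 to 0.7 that is assumed. At 0.3 the gain is modest, under 4 percentage points; every value in the range gives some gain. That the test is unadjusted is read from a single sentence in an article, without sight of the full analysis plan.

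**What to change.** Replace the analysis sentence in Statistical design with wording such as: *The primary comparison is the baseline-adjusted mean difference between randomised arms in the QLQ-C30 global QoL score at [month 3, 6, 9 or 12], tested two-sided at 5%, from ANCOVA, or from a repeated-measures model over the 3-monthly visits, with baseline score as covariate.* The sponsor should choose one visit and one model before any outcome comparison by arm. The visit has to be named because the analysis sentence gives none and the adjusted comparison needs one. The global scale is the one used for sizing. A simple change-score test should not be substituted.

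For patients still to be enrolled, have the baseline questionnaire completed before randomisation, if this is not already done. Study procedures requires only that it precede treatment, and the schedule figures that might show the order are not visible here. This rule cannot reach the 63 patients already randomised according to Trial status.

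The cost is one paragraph of analysis wording and one line on timing. No new assessments are needed and the sample size stays at 144.
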